### Diagram of the patient pathway

##

**Identification of the patient included in the observatory**

**Paediatrician invites the child + parents**

Inclusion

**6**

**6**

**M**

**O**

**N**

**THS**

**Enrolment consultation** (at least one hour)

Clinical examination and collection of the pathway followed by the child

**If the patient is already being monitored:**

Recovery of the assessments ± proposal of study tests if any are missing

**If the patient is not being monitored**:

Organisation of four visits with specialists within six months (max)

ENT Audiometry

Ophthalmologist

Psychologist

Tests according to age

Speech therapist

Tests according to age

Completion of the IES-R self-questionnaire

by the parents

Recovery of the results/assessments of the various specialists

**End of study consultation**

Inform parents and child about the assessments performed

### Visit details

- **Enrolment visit**

This enrolment consultation with the investigating paediatrician will last at least one hour and will include:

- An interview regarding the meningitis-related to the meningitis (skin sequelae, hospitalisations since the meningitis) and any follow-ups.
- General clinical, orthopaedic and skin examinations.
- Neurological examination.
- The follow-up information will be collected by the recruiting site: consultation/hospitalisation assessments and imaging reports (brain MRI, if performed).
- Child‘s school history, screening for learning disability.
- **Specialised assessments, a maximum of four**

The purpose of the specialised assessments is to assess possible sensory sequelae:

- ENT assessment and audiometry.
- Vision assessed by an ophthalmologist.
- Screening for oral and written speech disorders by a speech therapist.
- The child’s intellectual development will be assessed using the WISC IV or V performed by a psychologist. If the WISC cannot be performed (too significant a retardation), the Vineland scale will be used to assess the child’s development.

If the child is not being monitored by one or more specialists, a list of professionals will be provided to the child’s parents for an appointment within six months of the enrolment visit.

If the child is being monitored, the findings from previous assessments will be collected and, if needed, completed by the professional monitoring the child.

- **End of study visit with the referring paediatrician**

This visit will allow the hospital physician monitoring the child to review the situation with the parents and provide feedback on the specialised assessments and possible management.

*Assessment of parental post-traumatic stress*:

Parental post-traumatic stress will be assessed through the Impact of Event Scale-Revisited (IES-R) questionnaire. The parents will be able to complete this questionnaire online through a dedicated site.

### Visit schedule

| Procedure/examination | Inclusion | 6-month period | End of study visit |
| --- | --- | --- | --- |
| Signing of the informed consent form | (*)✓ |  |  |
| Paediatric/neurological assessment | ✓ |  | (*)✓ |
| Psychological assessment |  | ✓ |  |
| Speech therapy assessment |  | ✓ |  |
| ENT consultation (audiometry) |  | ✓ |  |
| Ophthalmology consultation (vision) |  | ✓ |  |
| Assessment of parental post-traumatic stress |  |  | (*)✓ |

*(*) These procedures/examinations are performed within the context of the research and not performed during routine clinical practice*

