- - The **Vineland Scale** (behavioural assessment) can be performed for all ages and will be proposed for children for whom the WISC or WPPSI cannot be performed. Development will be measured on a development scale based on an interview with the parents.

Developmental age and standard deviation compared with chronological age.

Assessment duration: at least 1.5 hrs.

- **Ophthalmology assessment**

The examination will determine the presence of refraction disorders, strabismus,

amblyopia and/or ocular motor disorders.

An orthoptic assessment may potentially be necessary if it is prescribed by the ophthalmologist.

Assessment duration: 20 mins.

- **ENT assessment**

Performance of an audiogram (to be repeated if the audiogram was done more than one year previously).

Assessment duration: 10 mins.

- **Assessment of parental post-traumatic stress**

The IES-R is a validated, 22-question, self-administered questionnaire in French. It assesses the parent’s experience of their child’s disease and identifies the presence of post-traumatic stress (total score ≥33).

This survey will be offered online.

Research schedule:

| Enrolment start date: | Q4 2020 |
| --- | --- |
| Enrolment duration: | 24 months |
| Patient follow-up end date: | Q4 2023 |
| Date of publication of results: | Q2 2024 |
| Duration of subject participation: | 12 months |

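### The protocol does not fix whether parents complete the IES-R before or after they are told their child's results, and the visit schedule and pathway diagram point to different times.

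*Protocol*

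**What the plan says.** Five parts of the protocol bear on when parents complete the IES-R.

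- **Visit schedule (8.2.3).** The row "Assessment of parental post-traumatic stress" has one tick, in the end-of-study column. The inclusion and six-month cells are empty.
- **Pathway diagram (8.2.1).** After the four specialist visits the text lists "Completion of the IES-R self-questionnaire" by the parents, then "Recovery of the results/assessments of the various specialists", and then the end-of-study consultation, whose content is "Inform parents and child about the assessments performed".
- **Visit details (8.2.2).** The end-of-study visit lets the physician "review the situation with the parents and provide feedback on the specialised assessments and possible management". The IES-R follows under its own sub-heading, without a date: "The parents will be able to complete this questionnaire online through a dedicated site".
- **Assessment details (8.2.4).** The IES-R "identifies the presence of post-traumatic stress (total score ≥33"), and it is again described as offered online.
- **Objectives and endpoints (5.2 and 7.1.2).** The objective is parental stress over the medium to long term. The endpoint names the instrument and gives no time point.

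**The concern.** The end-of-study visit exists to give parents results on intellect, language, hearing and vision. The protocol expects some of these to be new to the family: section 4.1 reports that some children had sequelae not recognised at discharge, and section 4.4 presents finding such sequelae as a benefit of taking part.

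A parent who answers a stress questionnaire after learning of a new deficit may be reporting, in part, a reaction to that news. The news goes mainly to families whose child has a newly found sequela. If completion falls before feedback for some families and after it for others, two things are at risk. The share of parents at or above 33 may depend on when they happened to answer. Any association between parental stress and the child's sequelae may be partly produced by the study's own feedback. If the completion date is not recorded, the analysis cannot separate the two.

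**Working it through.** No formula in the protocol governs this point and there is no stated figure to reproduce. The check is a comparison of sections.

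**Step 1: which visit?** Section 8.2.3 gives the end-of-study visit only. The diagram text in 8.2.1 gives a step after the specialist visits and before results are recovered. If the diagram's order is as extracted, the six-month column of 8.2.3 should carry the tick, and it is empty. The two do not agree as written.

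**Step 2: what happens at the end-of-study visit?** Sections 8.2.1 and 8.2.2 agree that parents are given the findings there.

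**Step 3: is the order relative to feedback fixed anywhere?**

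| Section | What it fixes | Order relative to feedback |
|---|---|---|
| 7.1.2 Secondary endpoints | Instrument | Not stated |
| 8.2.1 Diagram | Position in a sequence | Before, if the extracted order is the layout |
| 8.2.2 Visit details | Online completion | Not stated |
| 8.2.3 Visit schedule | Visit | Not stated within the visit |
| 8.2.4 Assessment details | Instrument, cut-off, online | Not stated |

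Only the diagram implies an order, and the schedule table does not follow it. Sites could read the protocol either way.

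**Step 4: can a size be given?** Not from the protocol. It has no IES-R mean, standard deviation, expected prevalence or feedback effect. The following is only an illustration, and every input except the cut-off of 33 and the 100 children is assumed: normal scores, SD 15 to 20, and a shift of 4 points in parents who answer after bad news.

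- Let p be the share at or above 33 without feedback, and z the normal quantile with upper tail p. After the shift the share is 1 − Φ(z − 4/SD).
- For p = 20%, z = 0.842. With SD 15: 1 − Φ(0.575) = 28.3%. With SD 20: 1 − Φ(0.642) = 26.1%.
- Those figures would need every parent to be affected. If 30% were affected (also assumed), the overall share is 20% + 0.30 × (28.3% − 20%) = 22.5% for SD 15, and 20% + 0.30 × (26.1% − 20%) = 21.8% for SD 20.
- For comparison, with about 100 children (6.3) and one respondent per child, the 95% half-width around 20% is 1.96 × √(0.20 × 0.80 / 100) = 7.8 points.

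Under these assumptions the overall prevalence moves by about 2 points, well inside its sampling error. Within the affected families the movement would be about 6 to 8 points, so a comparison by sequela status is more exposed than the overall figure.

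**The case against.** The strongest reply is that the sections can be read together. The table names a visit, not the order within it. Online completion could come before the consultation and simply be logged in the last column. The diagram, the only place with a sequence, puts the IES-R before feedback. That reading is possible, and it is why bias is not established. But the protocol does not require it, and a site working from the table alone would have no reason to send the link early.

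The diagram also survives only as extracted text. Its order is likely rather than certain evidence of the layout, and the IES-R line follows the branch for children not already monitored. This weakens the contradiction. It does not remove the gap, because the table alone ties the questionnaire to the feedback visit and sets no order.

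The objective in 5.2 does not exclude stress arising from the child's sequelae. That is fair: such stress is part of what is being measured. A reaction to findings disclosed by the study days or minutes earlier is a different quantity, and it would be present only for parents who answered late.

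Three stronger conclusions might be inferred, and the documents do not support them:

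- **That the score does mix disease and feedback effects.** The order is unfixed, so it may; nothing shows that it will.
- **That families who leave early will have no IES-R.** Online completion is not made conditional on attending the last visit, and 10.1 keeps data already collected from families who leave.
- **That prevalence would rise by 6 to 8 points overall.** That needs an unsourced shift applied to every parent, although only parents given new bad news would plausibly be affected.

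**Conclusion.** The point holds as a gap in timing. The schedule places the IES-R at the visit where results are fed back, the diagram text places it before, and no section fixes the order. The score may therefore capture reaction to new findings in some families, mainly those with newly found sequelae.

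The possible bias has no size that can be derived from the protocol, and the illustration above rests on assumed inputs. The consequence is limited to a descriptive secondary endpoint; the primary endpoint and the target of about 100 children are untouched. It still deserves correction in the protocol, because it concerns when data are collected and a later analysis cannot restore a time point that was neither fixed nor recorded.

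**What to change.** Reconcile 8.2.1, 8.2.2 and 8.2.3 to one IES-R time point that precedes feedback. For example, send the online link at or soon after inclusion and ask for completion before the end-of-study consultation. Inclusion is one option; any point clearly before feedback would do. Move the tick in the schedule table to match.

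Record the date on which the questionnaire is completed, so that it can be set against the date of the consultation. Report questionnaires completed after feedback separately or in a sensitivity analysis, and do not discard them.

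The cost is one extra date field and an earlier link, with no added visit. The change reduces the problem without removing it: parents may still hear findings directly from the specialists, and parents of children already being followed may know them from earlier care.

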### Details of the study assessments and evaluations

If the child’s assessments and/or examinations were performed more than one year previously, they will be repeated.

- **Paediatric assessment**

Detailed interview, general clinical, skin, orthopaedic and neurological examinations. Medical and education history, type of follow-up implemented.

- **Speech therapy assessment**

Various tests will be proposed to the child according to their age

- Under four years of age: **EVALO 2-6,** a battery of oral language development tests for children from 2 years and 3 months to 6 years and 3 months.

There are two versions of this: the “small“ version for up to 4 years and 3 months and the “large“ version for older children. Using a range of tests grouped by subject, it explores various skills separately (linguistic skills, pragmatic skills, functional architecture of language), which test both expression and comprehension.

- Above four years of age: **EXALANG battery of digital tests** on the HAPPYNEURON platform.

This is actually composed of five batteries of tests, which include an examination of oral language, written language and cross-sectional skills for children from 3 to 20 years.

It is divided into age groups: 3–6 years, 5–8 years, 8–11 years and 11–15 years.

Each battery of tests is randomised, so that the desired tests and the order in which they are used can be selected (there is no obligation to use an entire set). The tests are standardised.

This tool allows the data analysed to be coupled with the clinical observation. The results are stored on a secure and certified “health data“ server.

Assessment duration: 1.5 hrs.

- **Developmental/psychological assessment**

Various tests will be proposed to the child according to their age with a learning disability assessment as well as an assessment of cognitive disorders in order to establish a final score.

- - **WPPSI IV** (Between 2.5 and 6 years of age):

IQ test in several dimensions: verbal, visual-spatial comprehension, fluid reasoning, working memory and processing speed.

- - **WISC V** (From 6 years of age):

IQ test including a verbal comprehension index, visual-spatial index, fluid reasoning index, working memory index and a processing speed index.

A total score of ≤70 is associated with a mental retardation; a score between 70 and 130 is low to above-average intelligence; and above 130 is higher intellectual potential.

- - The **Vineland Scale** (behavioural assessment) can be performed for all ages and will be proposed for children for whom the WISC or WPPSI cannot be performed. Development will be measured on a development scale based on an interview with the parents.

Developmental age and standard deviation compared with chronological age.

Assessment duration: at least 1.5 hrs.

- **Ophthalmology assessment**

The examination will determine the presence of refraction disorders, strabismus,

amblyopia and/or ocular motor disorders.

An orthoptic assessment may potentially be necessary if it is prescribed by the ophthalmologist.

Assessment duration: 20 mins.

- **ENT assessment**

Performance of an audiogram (to be repeated if the audiogram was done more than one year previously).

Assessment duration: 10 mins.

- **Assessment of parental post-traumatic stress**

The IES-R is a validated, 22-question, self-administered questionnaire in French. It assesses the parent’s experience of their child’s disease and identifies the presence of post-traumatic stress (total score ≥33).

This survey will be offered online.

Research schedule:

| Enrolment start date: | Q4 2020 |
| --- | --- |
| Enrolment duration: | 24 months |
| Patient follow-up end date: | Q4 2023 |
| Date of publication of results: | Q2 2024 |
| Duration of subject participation: | 12 months |

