# Subject screening

Inclusion criteria

- Infants and children 1 to 15 years of age;
- Who had meningitis or meningococcal purpura fulminans included in the observatory between 2010 and 2019;
- One of the individuals with parental authority has read and understood the information letter and their express consent has been obtained;
- Patient affiliated with a social security scheme (Social Security or Universal Medical Coverage).

Exclusion criteria

- Refusal of either parent.

Enrolment Objective

Approximately 100 patients are expected to be enrolled in the study.

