# Research methodology

This is an interventional study with minimal risks and obligations involving human subjects (RiPH2).

It is a multi-centre, prospective, non-randomised study.

Primary and secondary endpoints

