### Secondary endpoint(s)

- Number of children who underwent a “flagged“ care pathway with the establishment of a score based on the consultations performed.
- Number of children with some severe neurological sequelae: hemiplegia etc.
- Number of children with orthopaedic complications (amputations etc.).
- Number of children with sensory disorders.
- Number of children with skin sequelae.
- Number of children with learning disabilities (with no identified neurological sequelae).
- Number of children with cognitive or psychological impairments identified on the WPPSI, WISC V or VINELAND. Care pathway followed by the children: number and type of follow-up consultations; Specialised paediatric consultations or not; ENT and speech therapy assessment/follow-up; neuro-developmental assessment.
- Parental post-traumatic stress assessment via the IES-R questionnaire.

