# Statistical aspects

Assessment of the number of subjects to be recruited

Between 2010 and 2019, 169 cases of meningitis and meningococcal purpura fulminans were declared in the French National Observatory of Bacterial Meningitis in Children. The initial clinical data for these patients are already known. After having excluded deceased patients (n = 9) and patients who have been lost to follow-up (approximately 20%, n = 30), and with an envisaged acceptance rate of 80%, 100 patients should be enrolled and follow the care pathway established as part of the study.

Analyses

The proportion and confidence interval of children with sequelae will be described for the entire recruited cohort within each age group and according to the type of sequelae: neurological, orthopaedic, skin, sensory or developmental. The qualitative data will be described by their number and percentage. The quantitative data will be described by their median and standard deviation. Kaplan Meier survival curves will be drawn to determine the presence of sequelae at various times after meningitis. Comparison tests will be performed to determine the presence of sequelae according to their severity or the initial onset.

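### The cognitive endpoint is a count of impaired children with no threshold and no norm reference, so the stated figures alone cannot show whether cognition differs from expectation

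*Protocol*

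**What the plan says.** Protocol, Secondary endpoint(s), and likewise the Project summary, define the cognitive outcome as "Number of children with cognitive or psychological impairments identified on the WPPSI, WISC V or VINELAND". No score is named there as the boundary of impairment.

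Details of the study assessments and evaluations lists the WPPSI IV (2.5 to 6 years) and the WISC V (from 6 years), each with several index dimensions, and gives one reading rule for the total: "A total score of ≤70 is associated with a mental retardation; a score between 70 and 130 is low to above-average intelligence". Scores above 130 form a third band. The Vineland is used where an IQ test cannot be done and is read against the child's chronological age.

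The Analyses text under Statistical aspects plans proportions with confidence intervals by type of sequela, developmental sequelae included. For scores it says: "The quantitative data will be described by their median and standard deviation". The only comparisons stated are within the cohort, by severity or initial onset.

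On design and size: "It is a multi-centre, prospective, non-randomised study", and "Approximately 100 patients are expected to be enrolled in the study".

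**The concern.** The background section argues that late sequelae may be underestimated and that few prospective studies look at later neuropsychological development. Cognition is formally secondary, but it carries much of that rationale.

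Some children without any disease score 70 or below. A count of such children, or a median, means little until it is set beside what would be expected. With no control group described, the published norm of each test is the one reference that comes with the data, and no stated analysis uses it for the IQ scores. The banding is also coarse: totals of 75 and 125 fall in the same band. If the count at ≤70 became the main reading of cognition, a broad, moderate loss could pass unremarked.

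**Working it through.** **The plan's own figure.** The number 100 is a feasibility count. Inputs, all from Statistical aspects: 169 observatory cases, 9 deaths, a loss of about 20% (printed as 30 children) and 80% acceptance among the remainder. The stated result is "with an envisaged acceptance rate of 80%, 100 patients should be enrolled".
- Survivors: 169 − 9 = 160.
- Applying 20% loss and 80% acceptance: 160 × 0.80 × 0.80 = 102.4.
- Using the printed 30 lost: (160 − 30) × 0.80 = 104.

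Both agree with about 100. No power or precision is stated for cognition, so there is none to reproduce.

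**Assumptions, none in the protocol.** Norm mean 100 and SD 15 (the printed bands at 70 and 130 are symmetric about 100 and fit ±2 SD); 5% two-sided, or 2.5% in the upper tail for the counts; a uniform downward shift d; n = 100, with n = 60 in case many children have no IQ score.

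**Count at ≤70 against the norm rate.**
- Norm rate: Φ((70 − 100)/15) = Φ(−2) = 2.28%, or 2.3 children expected in 100.
- Exact binomial critical count at n = 100: 7 or more (upper tail 0.8%; 6 or more gives 2.7%, too large).
- With d = 5: Φ((70 − 95)/15) = Φ(−1.667) = 4.78%, or 4.8 children expected. P(X ≥ 7) = 20%. With the cut at 70.5 to allow for whole-number scores it is 25%.
- An observed 5/100 has an exact 95% CI of 1.6% to 11.3%, which includes the norm rate.

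**Count at ≤85 against the norm rate.** Norm rate Φ(−1) = 15.9%; under d = 5, Φ(−0.667) = 25.2%; critical count 24 at n = 100; power 65%.

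**Mean against the norm.** One-sample t test with noncentrality (d/15)√n. For d = 5 and n = 100 this is 3.33, and power is 91%. The 95% CI half-width is ±3.0 points at n = 100 and ±3.9 at n = 60.

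| Uniform shift, SD 15 | count ≤70 | count ≤85 | mean |
|---|---|---|---|
| 3 points, n = 100 | 7% | 28% | 51% |
| 5 points, n = 100 | 20% | 65% | 91% |
| 7.5 points, n = 100 | 50% | 95% | 99.9% |
| 5 points, n = 60 | 16% | 45% | 72% |

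**Sensitivity, n = 100, mean loss 5 points.**

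| Scenario | count ≤70 | mean |
|---|---|---|
| cohort SD 12 | under 1% | 98% |
| cohort SD 18 | 73% | 79% |
| cohort SD 20 | 91% | 70% |
| 20% of children lose 25 points, the rest none | 82% | 78% |

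In the last row the share at ≤70 is 0.8 × Φ(−2) + 0.2 × Φ(−5/15) = 9.2%, and the SD is √(225 + 0.2 × 0.8 × 25²) = 18.0.

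**The case against.** A reader might infer that cognition is judged only by a cut-off of 70. The protocol does not say so: the endpoint names no cut-off, and the sentence on scores explains how the test is read. What can be said is that impairment is left undefined and that the one low cut-off in print is an extreme one.

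A reader might also infer that the scores are thrown away. They are not. The planned median and SD would cover IQ totals, and a reader of the results could set the median beside the norm. With the normal approximation (SE 1.2533 × 15/√100 = 1.88), the median against 100 has about 76% power at 5 points and 98% at 7.5. The Vineland is age-referenced, and learning disability and language are assessed separately. But the protocol gives the median neither a reference value nor an interval.

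The protocol plans no test of the count against 2.3%; that comparison is supplied here to measure what a count can show. The background reports sequelae at the end of hospitalisation in 10 to 40% of cases, so harm concentrated in a minority is plausible, and there the count does as well as the mean or better. This stands, and it is the reason to report both.

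A statistical analysis plan, not shown, may add a norm comparison. That limits the point to what this protocol fixes: the form of the endpoint and the descriptive methods.

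**Conclusion.** The point holds in limited form. The stated cognitive outputs are a count with no threshold, plus a median and SD with no reference, in a cohort with no control group described. Alone, they cannot show whether these children differ from expectation.

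For a broad shift of 5 to 7.5 points with SD near 15, the mean against the norm is much more sensitive than a count at ≤70: about 91% against 20% at 5 points and 99.9% against 50% at 7.5 (n = 100). These figures rest on the assumed norm of 100/15 and on a uniform shift. The stronger statement, that the study would miss a moderate deficit, is not supported. The count has about 82% power at a uniform 10 points, and it matches or beats the mean when a badly affected minority widens the SD. This is a worthwhile, inexpensive improvement to a secondary endpoint and leaves the primary endpoint untouched.

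**What to change.** In Secondary endpoint(s) and Analyses:

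1. State what counts as impairment on each instrument. A total of exactly 70 now falls in two printed bands; assign it to one.
2. Keep the count. Show observed numbers at ≤70 and ≤85 beside those expected from the norm (2.3% and 15.9% under the assumption above).
3. Report mean full-scale IQ with a 95% CI against the published norm of the test and edition used.
4. Record why a child had the Vineland. Children too impaired for an IQ test count as below the cut-off and take the lowest rank in a rank-based sensitivity analysis; otherwise leaving them out raises the mean. Children below the WPPSI age range of 2.5 years, whom the lower age limit of 1 year admits, had no IQ test for another reason and should be reported separately.
5. First reconcile Visit details (WISC IV or V, no WPPSI) with Details of the study assessments and evaluations (WPPSI IV, WISC V), because the norm depends on the edition.

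The cost is wording; the scores are already collected. The limit to state is that a gap from the norm may also reflect selective participation (about 20% lost to follow-up, then 80% acceptance) and a norm population that differs from Ile de France.
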